**Figure 1 fig1:**
[figure not shown]
Visualization and analysis of key anatomical and physical parameters with implications for BPPV treatment. Pressure distribution on the walls of the membranous labyrinth during rotation around the Z-axis for **(a)** real and **(b)** ideally orthogonal semicircular canals. **(c)** Endolymphatic velocities in the posterior semicircular canal obtained during rotation around the Z-axis. A Poiseuille flow with an ampullifugal direction is observed. **(d)** Displacement of otoconia during the standard Epley maneuver. The otoconia exit the posterior semicircular canal but do not reach the utricular macula, indicating that the maneuver cannot be considered successful. Orientation of the horizontal semicircular canal relative to the Frankfurt plane (blue) for **(e)** an idealized model with orthogonal canals, **(f)** the bony labyrinth of the subject shown in the previous figures, and **(g)** the bony labyrinth of a patient refractory to standard treatment. The anomaly in the orientation of the semicircular canals may explain the ineffectiveness of the treatment.

Such models provide valuable insights into the underlying causes of BPPV and help optimize individualized treatment strategies for patients who do not respond to traditional maneuvers (22). For instance, Figures 1e–g highlight the significant deviation of the horizontal semicircular canal in a refractory patient compared to a healthy or idealized model. This anomaly may explain the ineffectiveness of the standard maneuvers for treating BPPV.

If the research hypothesis is correct, adjusting the head movement angles could tailor the repositioning maneuvers to each patient’s specific anatomy. This adaptation could be accurately implemented using a mechanized chair designed for high precision. This approach would enable faster symptom resolution, reduce healthcare costs (in terms of fewer repeated consultations), and shorten the duration of work and functional disability associated with persistent vertigo.

The main objective of the present study is to enhance the effectiveness in treating patients with refractory benign paroxysmal positional vertigo (BPPV) of the posterior semicircular canal through personalized otolith repositioning maneuvers (using a mechanized chair), tailored to the spatial arrangement of each patient’s semicircular canals. This will be compared with the repetition of conventional maneuvers and the use of Brandt-Daroff exercises.

The secondary objectives are:

To determine whether there are differences at the time of diagnosis (mainly in the characteristics of nystagmus) between patients with refractory BPPV and those who respond well to conventional maneuvers.To develop software capable of generating a mathematical model based on MRI images of the patient’s inner ear, predicting the movement angles necessary to guide the otoliths back to the vestibule. This model will also provide additional information that can be used to rule out or confirm the presence of other underlying pathologies.To quantify the potential reduction in the subjective perception of disability achieved by performing modified, personalized maneuvers compared to the repetition of conventional maneuvers and Brandt-Daroff exercises.To quantify the reduction in healthcare resources (primarily in the number of consultations) achieved through treatment with personalized maneuvers.

## Methods and analysis

2

### Study design

2.1

This is an experimental, multicenter, open-label, randomized study (using balanced block randomization) with two parallel arms. The study targets patients with a definitive diagnosis of refractory posterior semicircular canal BPPV (BPPVp).

### Study participants

2.2

*Study period*: From January 1, 2024, to December 31, 2026.

*Study population*: Patients diagnosed with BPPV.

*Target population*: Individuals >18 years of age, of both sexes, diagnosed with unilateral refractory BPPVp, from three Health Areas. Participants will be selected from patients attending the Otoneurology Unit of the Otolaryngology Departments of these three University Hospital Complexes.

*Inclusion criteria*: Participants must understand the study objectives, agree to participate, and sign the informed consent form. Candidates must meet the following two requirements:Diagnosed with BPPVp according to the Barany Society criteria:Recurrent episodes of vertigo or positional instability, triggered by lying down or turning the head in the supine position.Episodes lasting less than 1 min.Positional nystagmus observed after a latency period during the Dix-Hallpike test (DHT), with an upward vertical component and a torsional component (clockwise on the left side and counterclockwise on the right).Symptoms not explained by any other cause.Refractory to otolith repositioning maneuvers (Epley and/or Semont maneuvers), with persistence of symptoms after three attempts.

*Exclusion criteria*: Participants will be excluded if they have:Cognitive impairment that prevents understanding of their condition and the required procedures.Pathological conditions that hinder the execution of the maneuvers.BPPV involving canals other than the posterior canal or bilateral posterior canal involvement.Patients who fail to demonstrate two successful repetitions of Brandt-Daroff maneuvers when provided with one set of verbal instructions and once set of printed instructions.

To confirm the diagnosis and rule out other potential causes, all participants will undergo a complete otoneurological evaluation, including:

Otoscopy.Basic neurological examination.Observation of spontaneous nystagmus (with and without gaze fixation).Clinical head impulse test (vHIT), including video-assisted evaluation.Positional tests (DHT, McClure test, and head hyperextension), with videonystagmographic recording.Pure-tone audiometry.

In cases of refractory BPPV (lack of resolution after three therapeutic maneuvers), a magnetic resonance imaging (MRI) scan of the inner ears and posterior cranial fossa will be requested to rule out central neurological causes.

### Randomization

2.3

*Pre-selection visit (Visit − 1)*: Participants will undergo a comprehensive vestibular assessment to identify candidates with refractory BPPVp. The following tests will be included:

Video-assisted head impulse test (vHIT) to assess for other vestibular pathologies.Dix-Hallpike test (DHT) to confirm the diagnosis of BPPVp.McClure test to exclude horizontal canal BPPV.Head hyperextension test to exclude superior canal BPPV.Dizziness Handicap Inventory (DHI) questionnaire adapted to Spanish, assessing perceived disability due to vertigo. Patients complete it independently at each participating hospital. This ensures consistency in subjective outcome reporting across study sites, minimizing potential biases introduced by different evaluators.

For posterior canal BPPV, it will be verified in the medical record that three repositioning maneuvers (Epley and/or Semont) were performed without symptom resolution.

Eligible participants will be given a detailed explanation of the study objectives and procedures, and will receive the approved Patient Information Sheet (PIS) to provide informed consent.

### Randomization process

2.4

*Visit 0 (Randomization visit)*: After obtaining consent, participants will be randomized to one of the following study arms:

Control group: Participants will be advised to perform Brandt-Daroff exercises at home twice daily for 8 weeks. An MRI of the inner ear and posterior cranial fossa will also be requested. If the exercises are ineffective, repositioning maneuvers will be repeated biweekly until symptom resolution using a mechanical rotational chair, specifically the Thomas Richard Vitton (TRV) reposition chair.Study group: Participants will perform Brandt-Daroff exercises at home twice daily for 8 weeks. An MRI will be conducted, and based on the images, a personalized mathematical model will be created to modify the angles of the repositioning maneuver. If the exercises are ineffective, the personalized maneuver will be performed using a mechanized chair.

A balanced block randomization sequence with block size n = 10 will be generated by a member of the research team.

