One plausible explanation for the ineffectiveness of maneuvers in certain patients may be individual variations in the spatial arrangement of the semicircular canals. Typically, the canals form angles of approximately 90° relative to one another, and repositioning maneuvers are designed based on this anatomical assumption. However, it is well known that there are individual differences in the angles between these structures (15), potentially resulting in a mismatch between the patient’s anatomy and the movements used in standard maneuvers. A mathematical model indicating the exact anatomical arrangement of the semicircular canals and predicting the expected movement of otoliths would allow the maneuver to be tailored to the specific anatomy of each patient, essentially enabling personalized medicine.

For patients with refractory BPPV, imaging (specifically, magnetic resonance imaging of the posterior cranial fossa) is recommended to rule out a neurological cause (16). This MRI typically includes the internal ears of the patient. From a routine clinical MRI of the inner ear, a personalized mathematical model can be developed. This process involves several stages and has been successfully applied in the development of personalized therapies in other fields, such as Cardiology. Initially, the digital version of the MRI is used to create a 3D model representing the endolymphatic fluid container. From this, a mathematical model based on Navier–Stokes equations is developed and solved using Computational Fluid Dynamics (CFD) techniques.

CFD-based numerical simulations offer a non-invasive tool for analyzing the human vestibular system, capable of predicting experimentally observed behaviors. For example, they can estimate the transcupular pressure threshold below which the membranous labyrinth’s response ceases to be linear, known as the mechanical adaptation effect (17). This innovative approach provides insights into understanding various vestibular pathologies, such as the Tullio phenomenon (18) and Ménière’s disease (19).

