### Data collection

2.6

Even if intermediate visits are necessary, the following study visits will be conducted according to the protocol (with data recording):

Visit 1 (eight weeks after inclusion):

The Dix-Hallpike Test (DHT) will be performed with videonystagmographic recording. If positive:In the control group, the conventional Epley maneuver will be repeated using a mechanized chair.In the study group, a personalized Epley maneuver will be performed using a mechanized chair.

Visit 2 (ten weeks after inclusion):

The DHT will be repeated with videonystagmographic recording. If positive:In the control group, the conventional Epley maneuver will be repeated using a mechanized chair.In the study group, the personalized Epley maneuver will be repeated using a mechanized chair.These maneuvers (conventional for the control group and personalized for the study group) will be repeated every two weeks until resolution of symptoms (or up to a maximum of 8 repetitions).

Visit 3 (Six months after inclusion):

The following variables will be recorded:Dix-Hallpike Test (DHT) results (negative or positive).Dizziness Handicap Inventory (DHI) score.Number of consultations required for resolution.

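### The full analysis set admits only eligible patients, yet information bearing on eligibility arrives after open-label allocation; this conflicts with the stated intention-to-treat principle

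*Protocol article*

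**What the plan says.** **Eligibility (section 2.2).** The diagnostic criteria for inclusion contain "Symptoms not explained by any other cause". The exclusion criteria rule out involvement of other canals and bilateral posterior canal disease. For refractory cases, which means every participant, an MRI "scan of the inner ears and posterior cranial fossa will be requested to rule out central neurological causes". No time is given for that scan.

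**Before randomization (section 2.3).** Visit −1 lists the video head impulse test, Dix-Hallpike, McClure, head hyperextension and the Dizziness Handicap Inventory. The MRI is not listed. The section then continues: "Eligible participants will be given a detailed explanation of the study objectives and procedures".

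**Randomization (section 2.4).** "After obtaining consent, participants will be randomized to one of the following study arms". The MRI appears within the arm descriptions that follow: for controls "An MRI of the inner ear and posterior cranial fossa will also be requested", and for the study arm "An MRI will be conducted, and based on the images, a personalized mathematical model will be created".

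**Before the maneuvers (sections 2.6 and 2.9).** At Visit 1, eight weeks after inclusion, "The Dix-Hallpike Test (DHT) will be performed with videonystagmographic recording", and a positive result leads to the chair maneuver of the assigned arm. Section 2.9 describes a re-evaluation at the treating center before intervention, to check that the BPPV persists and is confined to the posterior canal.

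**Analysis (section 2.8).** The FAS is restricted to randomized, consenting patients who met all inclusion and no exclusion criteria. Intention to treat is stated as the governing principle.

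**The concern.** An eligibility-restricted FAS does little harm if eligibility is settled on information fixed before allocation. Here two pieces of relevant information are placed after it: the MRI, which bears on the inclusion criterion about other causes, and the re-evaluation, which bears on the exclusion criterion about other canals.

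The trial is open-label (section 2.1), and section 2.9 says the same person performs the maneuvers and evaluates the outcome. Whoever decides that a patient was not eligible after all may therefore know the arm, and possibly the response. Section 2.8 does not confine that decision to information from before randomization, nor does it ask for it to be made blind to arm. What is at stake is the randomized comparison that the intention-to-treat statement is meant to protect.

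**Working it through.** **Step 1: the texts side by side.**

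| Information | Criterion it bears on | When it arrives |
|---|---|---|
| Vestibular tests at Visit −1 (2.3) | BPPV of the posterior canal | Before randomization |
| MRI (2.4; purpose in 2.2) | Symptoms without another cause | Within each arm, after randomization |
| Re-evaluation before the maneuvers (2.9) | Posterior canal only | Before intervention; maneuvers start at Visit 1, so naturally read as after randomization |

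The FAS rule refers to all the criteria without saying as of when. Under it, a patient judged ineligible on the second or third row can leave the analysis. Under intention to treat, the same patient stays. The two statements in section 2.8 then give different analysis sets.

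**Step 2: the plan's own figure.** Inputs from section 2.10: 25% and 75%, two-sided alpha 0.05, power 95%. With pooled variance and no continuity correction,

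n = [1.960·√(2·0.5·0.5) + 1.645·√(0.25·0.75 + 0.75·0.25)]² / 0.5² = (1.386 + 1.007)² / 0.25 = 22.9, so 23 per arm.

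This agrees with the stated 23, whose power is 95.1%. The plan then enrolls 54 (27 per arm) for 15% dropout.

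**Step 3: effect on the estimated difference (illustration).** The documents give no rate of findings that would lead to removal, so k = 1 or 2 such patients per arm is an assumption. So is their being non-responders. The others respond at 75% and 25%, with n = 27 per arm. Keeping the k patients multiplies an arm's rate by (27 − k)/27; removing them restores the planned rate.

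| Handling | k = 1 | k = 2 |
|---|---|---|
| Kept in both arms (intention to treat) | 72.2 − 24.1 = 48.1 | 69.4 − 23.1 = 46.3 |
| Removed from both | 75.0 − 25.0 = 50.0 | 75.0 − 25.0 = 50.0 |
| Removed from study arm only | 75.0 − 24.1 = 50.9 | 75.0 − 23.1 = 51.9 |
| Removed from control arm only | 72.2 − 25.0 = 47.2 | 69.4 − 25.0 = 44.4 |

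Against the intention-to-treat result, the shift runs from −0.9 to +2.8 points for k = 1 and from −1.9 to +5.6 for k = 2. Against removal from both arms, removal from the study arm alone adds 0.9 or 1.9 points.

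**Step 4: power.** Dropout is taken first: 54 × 0.85 = 45.9 patients. A further assumed loss of 0%, 2%, 5% or 10% from the FAS leaves 45.9, 45.0, 43.6 or 41.3 in total. Power at 75% against 25% is then about 95.0%, 94.6%, 93.9% or 92.6%. Power is not the problem.

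**The case against.** The case on the other side has four parts.

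- **Timing of the MRI.** The trigger for the scan, failure of three maneuvers, is verified in the record before consent, and the Introduction says such imaging "is recommended to rule out a neurological cause". Some patients may arrive already scanned, and the arm descriptions could be read simply as what each arm receives. This is fair. But section 2.4 speaks of a scan still to be requested or conducted, and section 2.3 does not list one.
- **The chain is long.** A central cause would have to escape the otoneurological evaluation in section 2.2, be judged to explain the symptoms, and then be treated as a breach of an inclusion criterion. No exclusion criterion names an MRI result, and nothing says that a central finding revokes eligibility. This stands, and it is why the effect is put as possible and probably small.
- **The FAS conflict exists whatever the MRI timing.** True. It is therefore the core of the point. The MRI and the re-evaluation show how the conflict could become active.
- **No written step makes the maneuvers wait for the report.** An article may leave that to the full protocol. Section 2.2 states what the scan is for, and eight weeks pass before the first maneuver.

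A reader might go further and infer that patients could be harmed by chair maneuvers performed before the report is read. The documents do not support this. Every participant has already had three repositioning maneuvers, and nothing in the article says that chair maneuvers add risk in a patient with a central lesion. A reader might also infer that exclusions would favor the study arm, because its images are needed to build the model. The article does not say that the clinical report would be read differently by arm, so no direction can be claimed.

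**Conclusion.** The point holds as a minor one about the analysis set. Section 2.8 contains two statements that disagree whenever a randomized patient is later judged ineligible, and the trial's sequence places information relevant to that judgment after open-label allocation. The wording permits such removals. It does not show that they will happen.

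The size rests on assumed counts: with one or two non-responding patients per arm, the estimate moves by at most 5.6 points from the intention-to-treat value, against a planned difference of 50 points. The direction depends on which arm loses patients, which the documents leave open.

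**What to change.** **Main change (section 2.8).** Define the FAS as all randomized participants who gave consent, analysed in the arm to which they were randomized. Alternatively, allow exclusion only for a criterion whose status was fixed before randomization, judged by someone unaware of the arm. Findings that arise later, from the MRI or the re-evaluation, would be reported and could inform a sensitivity analysis. This is a wording amendment: no added procedure and no delay.

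**Low-cost addition (sections 2.3 and 2.4).** Where feasible, obtain the planned MRI after consent and before randomization, using the sequence required in section 2.7 so that one scan serves both purposes, and have the clinical report available. If that is not feasible, have the report available in both arms before the first maneuver at Visit 1. No scans are added for enrolled patients, since both arms already have one planned. The downsides are a possible delay, whose length cannot be stated because the documents give no MRI waiting time, and a few candidates scanned but not enrolled. Whether the fallback fits within the eight weeks of exercises depends on the same unknown.

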### Study limitations, data biases, and mitigation strategies

2.9

Despite being an open-label study, the potential bias introduced is minimal, as both the maneuvers and outcome evaluation are performed by the same person. The primary outcome (resolution of nystagmus) is assessed objectively through videonystagmography, which does not require interpretation by the evaluator.

There is a risk of patient dropout during the eight-week period of Brandt-Daroff exercises prior to the personalized maneuver. To mitigate this risk, patient adherence will be closely monitored and encouraged with reminders and follow-ups.

Since patients will be recruited from three different hospitals, there may be diagnostic biases depending on the evaluator. However, all intervention maneuvers (both personalized and conventional) will be conducted at a single center, where a diagnostic reevaluation will be performed prior to intervention to confirm that the BPPV remains unresolved and exclusively affects the posterior canal.

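### A single published block size of 10 in an open-label trial lets anyone who knows the whole allocation history deduce the end of each block, and list generation is not separated from enrolment

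*Protocol article*

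**What the plan says.** Section 2.1 (Study design) states: "This is an experimental, multicenter, open-label, randomized study (using balanced block randomization) with two parallel arms". Section 2.4 (Randomization process) gives the allocation rule in one sentence: "A balanced block randomization sequence with block size" 10 "will be generated by a member of the research team". The same section places allocation at Visit 0: "After obtaining consent, participants will be randomized to one of the following study arms".

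Three statements in section 2.9 (limitations and biases) bear on who can know what. Recruitment is spread over sites ("Since patients will be recruited from three different hospitals"). All maneuvers in both arms take place at one center. For those maneuvers, "both the maneuvers and outcome evaluation are performed by the same person".

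The article does not say whether there is one list or one per hospital, who holds it, or whether the person who prepares it also enrols patients.

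**The concern.** Blocking protects balance, but in an open-label trial it leaks information. Once five patients in a block of 10 have gone to one arm, the rest of that block is determined. The size is constant and published, so block boundaries can be counted. An enroller who knows that the next place is control, or study, can bring a patient forward, hold one back, or read a borderline criterion strictly.

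Some room for this exists. Section 2.2 excludes conditions that hinder the maneuvers, which takes judgement, and the timing of an approach to a patient is always discretionary. The objective videonystagmographic endpoint protects measurement of the outcome; it does not protect the make-up of the arms. Section 2.9 discusses open-label, dropout and diagnostic bias, but not selection at entry.

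Selection bias cannot be reliably repaired in the analysis, and the trial is small. With 27 per arm, each outcome changed by steering moves the observed difference by 1/27 = 3.7 percentage points.

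**Working it through.** **Inputs.** Block size 10, taken as 5:5 (sections 2.1 and 2.4). Total 54, 27 per arm (section 2.10). Three recruiting hospitals (sections 2.2 and 2.9).

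**The plan's own figure.** The article gives no figure on predictability. Its sample size reproduces: for 25% versus 75%, two-sided alpha 0.05 and 95% power, with pooled variance,

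n = [1.960·√(2·0.5·0.5) + 1.645·√(0.25·0.75 + 0.75·0.25)]² / 0.5² = (1.386 + 1.007)² / 0.25 ≈ 22.9, so 23 per arm.

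Then 46/0.85 = 54.1, stated as 54. I use N = 54 below.

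**Certain allocations per block.** A place is certain when all remaining places belong to one arm. With k places left, the probability is 2·C(10−k, 5)/C(10, 5):

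| Place in block | Places left, k | Probability of certainty |
|---|---|---|
| 10th | 1 | 2·126/252 = 1.000 |
| 9th | 2 | 2·56/252 = 0.444 |
| 8th | 3 | 2·21/252 = 0.167 |
| 7th | 4 | 2·6/252 = 0.048 |
| 6th | 5 | 2·1/252 = 0.008 |

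The sum is 1.67 per block, in agreement with 2m/(m+1) = 10/6 for m = 5. The first five places are never certain.

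**Over 54 patients.**
- *One shared list, full history known:* five full blocks plus four patients. The last four can never be certain, so the expected number is 5 × 1.67 = 8.3 (15%), with a minimum of 5.
- *One list per hospital, 18 each (assumption):* one full block plus eight places each, so 3 × (1.667 + 0.167 + 0.048 + 0.008) = 5.7.
- *One shared list, hospital sees only its own patients:* certainty requires five same-arm allocations at that hospital within one block. Simulation with patients split evenly at random gives well under 1 of 54.

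**Best guess.** Always guessing the arm with more places left is right m + (4^m/C(2m, m) − 1)/2 times per block: 5 + (1024/252 − 1)/2 = 6.53 of 10 (65%), against 50% by chance. Over 54 on one list it is about 34.9 (65%).

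**Alternatives, simulated over 54 patients.**

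| Scheme | Best guess correct | Certain allocations |
|---|---|---|
| Fixed 10, size known | 65% | 8.3 |
| Random 8/10/12 | 65% | about 0.8, even if the set of sizes leaked |
| Random 4/6 | 69% | about 3, if the set of sizes leaked |

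For comparison, fixed blocks of 4 give 71% correct guesses with 33% certain, and fixed blocks of 6 give 68% with 25% certain. A block of 10 is therefore not a poor size; the weakness is that it is single and disclosed.

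**The case against.** Several parts of the opposing case stand.

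- **Role overlap.** A reader might infer that the list is made by the people who recruit, treat and assess, so that the list holder knows every allocation. The article does not say this. The team also includes those doing the MRI reconstruction and fluid simulation, and the only overlap stated is between performing maneuvers and evaluating outcome. Full foreknowledge would follow only if the generator enrols or shares the list.
- **Concealment.** A reader might take the silence on concealment to mean that there was none. A condensed article commonly leaves this to the full protocol, so the silence is no finding, and independent release may already be in place.
- **Breadth.** A reader might conclude that upcoming allocations are generally predictable, or scale 16.7% to 9 of 54. Some 85% are not certain even in the worst case on one list, and the incomplete sixth block brings the count to 8.3.
- **Eligibility.** Several entry criteria have documented rules: the failed maneuvers are checked in the medical record, diagnosis follows published criteria, and the exercise demonstration has a stated pass rule. The room for steering is narrower than it may seem.
- **Visibility.** With three hospitals and a shared list, one site's recruiter would rarely reach certainty.

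The last point is weakened by the trial's structure. Maneuvers for both arms are done at one center, and each study-group patient needs an individual model, so the central team can learn allocations across hospitals. The treating person may learn them up to eight weeks late, and not at all for patients who resolve or drop out first. Accrual is slow: 54 patients in roughly 30 months (a 36-month study period less six months of follow-up) is 1.8 per month. A tally is feasible, although nothing shows that anyone keeps one.

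**Conclusion.** The point holds in a limited form. The stated rule, a single disclosed block size in an open-label trial, makes on average 1.67 of every 10 allocations certain to a person who knows the full history of the list. That is about 8 of 54 on one shared list, about 6 on three hospital lists of 18, and few for a hospital that sees only its own patients. The remaining places can be guessed only moderately better than chance.

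The size rests on three assumptions: 5:5 blocks, knowledge of every earlier allocation on the list, and a list structure that the article does not state. As a ceiling only, 8 steered places that each changed an outcome would move the difference by 8 × 3.7 ≈ 30 points, against the planned 50. That is not an expectation, since nothing in the documents suggests that steering occurs.

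Who generates the list is a gap in the stated separation of roles, not evidence of a breach. I rate the whole as a cheap improvement.

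**What to change.** For the part of the sequence not yet used:

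1. Replace the fixed block of 10 with randomly varied block sizes of similar length, for example 8, 10 and 12, and do not disclose the sizes to recruiters. Avoid a 4/6 mix, which would raise the best-guess rate to about 69%.
2. Have the sequence generated and held by someone with no role in recruitment, treatment or assessment.
3. Release each allocation only after consent and baseline assessment are complete.
4. State in the protocol whether there is one list or one per hospital.

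If the full protocol already provides for items 2 and 3, only the block sizes need to change. If enrolment is complete, report who generated and held the list and whether that person recruited, treated or assessed.

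The cost is a minor amendment, with no change in sample size. The arms may end a few patients apart, particularly if a block is abandoned part-way. The present scheme does not guarantee 27:27 either: 54 is not a multiple of 10, and on one list exact balance has probability C(5,2)·C(5,2)/C(10,4) = 100/210 = 48%. Varied sizes remove most of the certain predictions but leave the guess rate unchanged, so independent generation and late release carry much of the protection.
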